## Abstract

**Background:**

The prognosis for patients with advanced epithelial ovarian cancer remains poor despite aggressive surgical resection and platinum-based chemotherapy. More than 60% of patients will develop recurrent disease, principally intraperitoneal, and die within 5 years. The use of whole abdominal irradiation (WAI) as consolidation therapy would appear to be a logical strategy given its ability to sterilize small tumour volumes. Despite the clinically proven efficacy of whole abdominal irradiation, the use of radiotherapy in ovarian cancer has profoundly decreased mainly due to high treatment-related toxicity. Modern intensity-modulated radiation therapy (IMRT) could allow to spare kidneys, liver, and bone marrow while still adequately covering the peritoneal cavity with a homogenous dose.

**Methods/Design:**

The OVAR-IMRT-01 study is a single center pilot trial of a phase I/II study. Patients with advanced ovarian cancer stage FIGO III (R1 or R2< 1 cm) after surgical resection and platinum-based chemotherapy will be treated with whole abdomen irradiation as consolidation therapy using intensity modulated radiation therapy (IMRT) to a total dose of 30 Gy in 1.5 Gy fractions. A total of 8 patients will be included in this trial. For treatment planning bone marrow, kidneys, liver, spinal cord, vertebral bodies and pelvic bones are defined as organs at risk. The planning target volume includes the entire peritoneal cavity plus pelvic and para-aortic node regions.

**Discussion:**

The primary endpoint of the study is the evaluation of the feasibility of intensity-modulated WAI and the evaluation of the study protocol. Secondary endpoint is evaluation of the toxicity of intensity modulated WAI before continuing with the phase I/II study. The aim is to explore the potential of IMRT as a new method for WAI to decrease the dose to kidneys, liver, bone marrow while covering the peritoneal cavity with a homogenous dose, and to implement whole abdominal intensity-modulated radiotherapy into the adjuvant multimodal treatment concept of advanced ovarian cancer FIGO stage III.

## Background

Ovarian cancer remains the number one gynaecological killer in the western world [1]. Symptoms tend to be vague; hence ovarian cancer is often detected late [2,3]. Approximately 70% of ovarian cancer patients present with advanced stage disease after it has spread beyond the genital organs and into the peritoneal cavity (stage FIGO III) or even further (stage FIGO IV, distant metastases). With a 5-year survival about 70% of patients with ovarian cancer stage II, the overall survival dramatically decreases in the advanced stages of disease, in stage III and IV it is only about 31% and 13% respectively [4,5].

The standard management of ovarian carcinoma is aggressive surgical resection (including at least total abdominal hysterectomy, bilateral adnexectomy, omentectomy, debulking of tumour masses) followed by platinum-based adjuvant chemotherapy. Generally this includes 6 courses of carboplatin or cisplatin (AUC 5) IV and paclitaxel (175 mg/m2) IV, every 3 weeks [6-11]. While the majority of patients respond to treatment, most will relapse, principally intraperitoneal, resulting in 5-year survival rates for advanced disease of approximately 20–25% [12,13].

However, subgroups of patients profiting from an even more aggressive treatment can be identified according to prognostic criteria such as stage, residual disease and grading. Patients with FIGO stage III G2/G3 with residual disease < 2 cm and FIGO stage II G3 R<2 cm are classified as high risk, with a risk of recurrence of around 80% with a 5-year survival of 25 % [14]. Hence, this subgroup of patients needs further efforts to improve outcome.

By now, several sometimes randomized trials have evaluated strategies of consolidation therapy for high risk patients (continuation of chemotherapy, other chemotherapy, high-dose chemotherapy followed by stem cell transplant, intraperitoneal chemotherapy, unspecific immunotherapy) but were not able to improve outcome significantly so far [5,9,10,15-17].

The use of whole abdominal irradiation (WAI) as a consolidation therapy would appear to be a logical strategy. The fact that whole abdominal radiotherapy can be curative in certain groups of patients has been shown by intensive studies by Dembo et al [18,19]. During the 1950s surgery and radiotherapy were the predominant treatment modalities in ovarian cancer. However, with the introduction of chemotherapy during the late 1950s and its proven effects in advanced ovarian cancer (yielding the best primary response rate), radiotherapy has been more and more abandoned mostly due to marked side effects [20]. Typically, a dose of 30 Gy is given to the whole abdomen with an anterior-posterior/posterior-anterior beam arrangement and posterior shielding of the kidneys [21]. Due to the extensive field sizes (40 cm × 30 cm or larger), a high percentage of patients experienced severe side effects, myelosuppression being the most commonly reported. Moreover, the shielding of organs at risk delivers inadequate low doses in parts of the target volume thus reducing efficiency of radiation [22-25].

Postoperative radiotherapy as a consolidation treatment with or without prior chemotherapy been investigated on numerous occasions, though initially with inconsistent and often disappointing results [26,27]. Thomas reviewed whole-abdominal pelvic irradiation in 28 published trials prior to 1992 [28,29]. Even though 700 patients were treated overall in these trials, it was impossible to reach a definitive conclusion as to the role of whole-abdominal irradiation for consolidation because of the diversity of criteria for patient selection, and the variability in the chemotherapy, surgery and radiation technique. Thomas gave some possible causes for these disappointing results in order to guide the design for future studies, the first being inappropriate patient selection based on large-volume residuum. Some authors suggest the initial residuum prior to chemotherapy should be less than 2 cm [26]. Most authors believe that radiotherapy should follow surgery and chemotherapy in case of small residual tumours (< 5 mm) or only microscopically detectable rests [30].

In addition to inappropriate patient selection, another possible explanation for the treatment failure observed in these trials is the high-degree of toxicity resulting in delayed or incomplete radiotherapy. Cumulative bone marrow toxicity is also increased in patients receiving additional chemotherapy. Inability to complete sequential therapy as planned in a significant proportion of patients may be a contributing factor to the lack of overall benefit [20,25,29]. Thus, if sequential multimodality therapy is to be tested, it is important to keep the risk of complications to a minimum maximising the probability of completing radiotherapy successfully. Severe late intestinal radiation reactions were recorded in about 10% [28]. These were associated with additional pelvic boost and previous second-look laparotomy, which is nowadays obsolete.

Recent studies have shown more promising findings. 1999 a retrospective case control study compared the outcome of patients with advanced ovarian cancer after surgery followed by chemotherapy with the combination of surgery, chemotherapy and irradiation. The results showed a significantly improved disease-free survival for patients in the radiotherapy group, and suggested that the role of radiotherapy should be re-evaluated in a prospective randomized study [30].

Also in 1999, results from 64 patients with advanced ovarian cancer without residual disease after surgery and carboplatin-based chemotherapy were randomized to either chemotherapy alone or chemotherapy plus consolidation radiotherapy. There was a significantly prolonged relapse-free interval and the overall survival in the radiotherapy arm in this study with differences being more pronounced in patients with FIGO stage III [31].

2003 a randomized trial compared whole abdominal radiation therapy, chemotherapy and no further treatment in advanced ovarian cancer (FIGO III). One hundred seventy-two patients achieved a complete surgical remission after induction chemotherapy. In the subgroup with complete pathologic remission, progression-free survival was significantly better in patients treated with radiotherapy (56% at 5 years) than with chemotherapy alone (36% at 5 years), and the untreated control group (35% at 5 years). Overall survival was also most favourable in the radiotherapy group (69% at 5 years), however, this difference failed to achieve statistical significance (P = 0,084). The number of recurrences was also lowest in the radiotherapy group. In the subgroup with microscopic residual disease, there was no significant difference in survival between the radiotherapy and chemotherapy group [32].

One trial published in 2005 aimed to determine the outcome associated with the use of whole abdominal radiotherapy in women with ovarian cancer, even after positive second-look laparotomy (SLL) or second look debulking for recurrent disease. The investigators came to the conclusion that radiotherapy appeared to be an efficacious treatment option for patients with microscopic disease at SLL, but does not appear to be more effective than chemotherapy in patients with macroscopic disease at SLL [33].

2003 a swedish systematic review of radiation therapy trials came to the conclusion there might be some evidence to suggest that radiotherapy plays a role as consolidation therapy in patients with advanced ovarian cancer and pathologically complete response after chemotherapy [34].

In summary, the review of available literature demonstrates a rationale in favour of consolidation whole abdominal irradiation in advanced ovarian cancer. Whole abdominal irradiation after surgical resection and platinum-based adjuvant chemotherapy seems to increase disease-free and overall survival in patients with ovarian cancer disease stage FIGO III with no or only minimal residual disease. However, classical WAI technique after surgery and chemotherapy is associated with high toxicities, particularly haematological toxicity, which leads to treatment interruptions.

Technical developments in radiotherapy techniques like intensity-modulated radiation therapy (IMRT) have now the potential to spare organs at risk (OARs) as kidneys, liver, and bone marrow [35,36]. Hence, these techniques might significantly decrease the toxicity while still adequately covering the peritoneal cavity with a homogenous dose [37]. Intensity-modulated radiation therapy (IMRT) is a relatively new but increasingly accepted technology delivering radiation more precisely to the tumour while sparing surrounding normal tissue [18,19,21,22,38-40]. Treatment planning and delivery with IMRT are a standard treatment technique now used for sites such as prostate, paraspinal tumours, tumours of the brain, and head&neck tumours. This technique is also increasingly explored for more challenging sites like gastro-intestinal tumours or breast cancer [35,41-48]. The challenge of this study is the application of this technique to a large and complexly shaped target volume like the peritoneal cavity [49,50].

Previous work by our group included inversely planned IMRT-treatments as a plan comparison based on CT-scans obtained from an abdominal staging CT scan of a patient with advanced ovarian cancer after receiving her informed consent. It could be shown that, in principle, IMRT of the whole peritoneal cavity is possible, though patient immobilisation using a vacuum mattress and a scotch cast mask was needed to obtain the required accuracy necessary in body stereotaxy.

## Methods/Design

### Study design

The study is designed as a single center pilot trial of a phase I/II study evaluating the feasibility and toxicity of intensity-modulated WAI.

### Study objectives

The primary objective is to evaluate the feasibility of planning and treatment application of intensity modulated whole abdominal irradiation and to evaluate the study protocol. Secondary endpoint is evaluation of the toxicity in intensity-modulated whole abdominal irradiation before the initiation of a prospective phase I/II study.

### Trial organisation

OVAR-IMRT-01 has been designed by the study initiators at the Department of Radiation Oncology at the University of Heidelberg. The trial is carried out by the Department of Radiation Oncology at the University of Heidelberg in co-operation with the German Cancer Research Center (dkfz) and Department of Gynaecology and Obstetrics.

### Coordination

The overall coordination is performed by the Department of Radiation Oncology at the University of Heidelberg. This department is also responsible for the overall trial management, database management, quality assurance including monitoring and reporting.

### Investigators

The study investigators are experienced radiation oncologists specialized in the treatment of patients with gynaecological malignancies. Patients will be recruited and treated by the physicians of the Department of Radiation Oncology of the University of Heidelberg.

### Ethics, informed consent and safety

The final protocol was approved by the ethics committee of the University of Heidelberg, Heidelberg, Germany (Nr: 176/2005) and by an independent expert group of the German Society for Radio-oncology (DEGRO). This study complies with the Helsinki Declaration in its recent German version, the Medical Association code of conduct, the principles of Good Clinical Practice (GCP) and the Federal Data Protection Act. The trial will also be carried out in keeping with local legal and regulatory requirements. The medical secrecy and the Federal Data Protection Act will be followed. The ClinicalTrials.gov Protocol ID is NCT00527631.

### Patient selection

Inclusion criteria into the study protocol are:

- histologically confirmed ovarian cancer stage FIGO III

- grade 2 or 3

- maximal typical surgical resection (including at least total abdominal hysterectomy, bilateral adnexectomy, omentectomy, debulking of tumour masses)

- postoperative residual tumour of less than 1 cm (maximal diameter of largest tumour residual is 1 cm)

- adjuvant chemotherapy consisting of six courses of carboplatin/paclitaxel or carboplatin/docetaxel

- mplete remission after chemotherapy

- Karnofsky performance Score >60

- patients > 18 and < 75 years of age

- written informed consent

### Exclusion criteria

- stage FIGO I or II

- stage IV (distal metastasis) stage

- III R2 > 1 cm

- delayed wound healing post laparotomy

- obesity

- neutrophil count (ANC) < 2000/ml before radiotherapy

- platelets < 100000/ml

- connective tissue disease, sclerodermia

- clinically active renal, hepatic, cardiac, metabolic, respiratory, coagulation or haematopoietic disease

- participation in another clinical trial

- patient refusal

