### Statistical calculations for trial sample size

The primary objective is to evaluate the feasibility of planning and application of intensity-modulated whole abdominal irradiation. 8 patients will be included into the study. If planning and treatment application is not feasible for the first 5 patients the study will be discontinued.

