#### Pre-therapeutic examinations

According to the interdisciplinary guidelines for therapy of ovarian cancer all patients receive 6 cycles of chemotherapy followed by a complete staging including pelvic examination, transvaginal ultrasound, and tumour markers allowing for assessment of success of the primary therapy. Additionally, abdominal and pelvic CT-scans using intravenous contrast agent are carried out. Further pre-irradiation investigations include ECG, blood count, electrolytes, coagulation, as well as blood chemistry.

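### Both numeric blood-count exclusion limits are printed per ml, which makes them near-zero counts; very probably a unit misprint, to be checked against the full protocol and corrected

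*Protocol article*

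**What the plan says.** The protocol article, under Exclusion criteria, lists two numeric haematological limits: "neutrophil count (ANC) < 2000/ml before radiotherapy" and "platelets < 100000/ml". The same list has a third haematological item without a number: "clinically active renal, hepatic, cardiac, metabolic, respiratory, coagulation or haematopoietic disease".

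Under Pre-therapeutic examinations a blood count is required: "Further pre-irradiation investigations include ECG, blood count, electrolytes, coagulation, as well as blood chemistry". No count limit or unit is given there. Under Adverse events, toxicity is to be evaluated before treatment, weekly during irradiation and at follow-up, again without a limit. Under Indication, gynaecology, internal medicine and radiation oncology must all agree to the treatment.

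The Background explains why marrow reserve is relevant. On the older technique it says that "a high percentage of patients experienced severe side effects, myelosuppression being the most commonly reported". On prior treatment it says: "Cumulative bone marrow toxicity is also increased in patients receiving additional chemotherapy". It sums up the classical technique as having high toxicities, "particularly haematological toxicity, which leads to treatment interruptions".

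**The concern.** The printed unit turns each limit into a count that a patient fit enough to be considered for irradiation would hardly ever fall below. Taken at face value, the two criteria do not separate patients with adequate counts from patients with severely reduced ones.

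This bears on the trial's endpoints. Patient selection requires six courses of a carboplatin and taxane combination, so reduced counts at entry are a foreseeable problem. The primary objective is the feasibility of planning and delivering the irradiation, and toxicity is secondary. The trial is small ("8 patients will be included into the study"), so one patient whose treatment is interrupted for low counts is 1/8 = 12.5% of the sample, or 1/5 = 20% of the first five patients on whom the discontinuation rule rests.

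**Working it through.** The article derives neither limit from other quantities, so there is no figure to reproduce. The check is a unit conversion and a search for any other statement that would correct the unit.

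**Inputs**
- Neutrophil limit: 2000 per ml (Exclusion criteria).
- Platelet limit: 100000 per ml (Exclusion criteria).
- 1 ml = 1000 µl and 1 L = 1000 ml.
- Illustrative severe cytopenia, an assumption not taken from the article: neutrophils 100 to 500 per µl; platelets 10,000 to 25,000 per µl.

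**Conversion of the printed limits**
- Neutrophils: 2000 / 1000 = 2 per µl. Per litre: 2000 × 1000 = 2 × 10^6, which is 0.002 × 10^9/L.
- Platelets: 100000 / 1000 = 100 per µl. Per litre: 100000 × 1000 = 10^8, which is 0.1 × 10^9/L.

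**Comparison with the assumed cytopenic patient**

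| Count | Assumed value (per µl) | Printed limit (per µl) | Ratio |
|---|---|---|---|
| Neutrophils | 100 to 500 | 2 | 100/2 = 50 to 500/2 = 250 |
| Platelets | 10,000 to 25,000 | 100 | 10,000/100 = 100 to 25,000/100 = 250 |

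Across the assumed ranges, the patient stays above both printed limits by a factor of at least 50 and is excluded by neither.

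**Size of the probable slip.** If the numerals were meant per µl, each printed limit is too low by a factor of exactly 1000. The article never states that unit, so the factor rests on an inference.

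**Search for a correction elsewhere.** Pre-therapeutic examinations and Adverse events both call for pre-treatment blood work but set no limit. No other section states a neutrophil or platelet limit or uses another unit. Nothing in the article corrects the two lines.

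**The case against.** The strongest case on the other side is that this is a notation slip with little practical effect. The investigators are described as experienced radiation oncologists, and a limit of 2 neutrophils per µl is so implausible that such readers would very probably notice it. This stands as a comment on likely harm. It does not rescue the text, because the criterion then works only if the reader overrides what is printed.

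Second, other safeguards exist: the non-numeric exclusion of active haematopoietic or coagulation disease, the agreement of three specialties, and the blood count before irradiation. This also stands. A reader might infer that there is no effective haematological check before radiotherapy, and the article does not support that. None of these safeguards supplies a number, however, and the disease exclusion does not clearly cover low counts caused by chemotherapy.

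Third, the text was read by machine, and the neighbouring eligibility lists show damage such as a truncated word and a broken bullet. A lost micro sign cannot be ruled out, and one systematic substitution would affect both lines. Against this, both lines consistently print an ordinary unit and nothing marks a fault at that spot. Looking at the source would settle it.

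Two further inferences should be resisted. One is that myelosuppression was the main reason whole abdominal irradiation was given up. The Background attributes the decline to marked side effects in general and says separately that myelosuppression was the severe effect most often reported. The other is that existing cytopenia would confound the toxicity endpoint. Toxicity is also evaluated before treatment, so low counts at baseline should be on record and distinguishable.

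**Conclusion.** The concern holds for the two numeric limits and no further. As printed they equal 2 neutrophils and 100 platelets per µl, and read literally they would not exclude a severely cytopenic patient. The conversion is exact. The ratios of 50 to 250 for neutrophils and 100 to 250 for platelets depend on the assumed ranges. The factor of 1000 depends on the inference that the numerals were written for a count per µl.

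A reader might go further and conclude that severely cytopenic patients would in fact be enrolled, or that exactly none would be excluded. The article gives no distribution of counts and keeps other safeguards, and staff would probably recognise the slip, so neither conclusion follows. The error still deserves correction, because it sits in an operative eligibility threshold and could be carried into case report forms or the planned phase I/II study. The conclusion also assumes that the unit is printed in the source as it appears in the text reviewed.

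**What to change.** The sponsor should check the unit of both criteria against the approved full protocol and correct the two lines so that the printed limits are the intended ones. If the full protocol has the same unit, it needs the same correction, as does any eligibility form derived from it. No threshold value is proposed here; that choice belongs to the sponsor and the investigators.

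The cost is two corrected lines. No procedure, visit or patient is added, because the blood count is already part of the examinations before irradiation.

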### Statistical calculations for trial sample size

The primary objective is to evaluate the feasibility of planning and application of intensity-modulated whole abdominal irradiation. 8 patients will be included into the study. If planning and treatment application is not feasible for the first 5 patients the study will be discontinued.

### Adverse events

Radiotherapy-related toxicities will be assessed using the NCI Common Toxicity Criteria (CTC). Toxicity will be evaluated pre-treatment, weekly during radiation therapy (blood count, electrolytes, chemistry, clinical examination, patient visits) and at follow-up. Unacceptable toxicity is defined as unpredictable or irreversible grade 4 toxicity.

Expectable possible acute toxicities (up to 3 months post radiation therapy) are fatigue, loss of appetite, weight loss, skin toxicity (epitheliolysis, erythema, hyperpigmentation), nausea, vomiting, irritable bowel syndrome, diarrhea, intestinal bleeding, proctitis, dysuria, interstitial nephritis, hepatitis, pneumonitis, haematological toxicity with thrombocytopenia, leukocytopenia, anaemia. These symptoms can be medically treated and usually resolve within 2–3 weeks. However, transient parenteral nutrition and hydratation might be necessary in some cases. All acute toxicities should completely resolve within a few weeks after radiation therapy.

Late side effects are rare and are defined as symptoms appearing at least 3 months post radiation. These could include chronic diarrhea, malabsorbtive syndrome, chronic bladder inflammation, enterecolitis, strictures, fibroses, ulcers, chronic bleeding. Very rare symptoms are fistulation, perforation, peritonitis, intestinal necrosis, ileus necessitating surgical intervention resulting in intestinal resection/anus praeter formation. In literature reviews, severe late intestinal radiation reactions were recorded in about 10%, and were associated with pelvic boost and previous second-look laparotomy. However, patients with these risk factors are not included in this trial. Cardiac, pulmonary, hepatic and renal toxicity with accompanying renal dysfunction, teleangiectases, and spinal cord toxicities are unlikely with the dose and fractionation applied in the trial.

